### Concealment mechanism {16b}

Allocation is not concealed and will be revealed to both the participants and the researcher upon randomization.

### Implementation {16c}

Each hospital is equipped with a random staff. The account and password of the random staff are given to enter the random system (http://121.229.17.89:9080/IWRS/). Patients will receive a unique random number from random staff.

## Assignment of interventions: blinding

### Who will be blinded {17a}

In this study, it will be impossible to blind the participants and Tai Chi coaches. To minimize bias, study personnel, such as researchers who perform relevant tests and outcome evaluators, will not have permission of a central stochastic system. Group A will be used to identify the control group, and group B will be used to identify the Tai Chi group, thus blinding the statisticians and outcome evaluators.

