**Methods:**

This is a parallel-design, two-arm, analyst assessor-blinded, randomized controlled trial. A total of 226 stroke patients in the recovery phase will be recruited and assigned randomly to a control group or Tai Chi group at a 1:1 ratio. The patients in the Tai Chi group will perform the Tai Chi exercise. The patients in the control group will perform walking exercises. Patients in both groups will receive conventional treatments and healthy education. The primary outcomes will be VO_2peak_ and scores on the MOS item short form health survey (SF-36) scale. Secondary outcomes will include vital capacity (VC), ejection fractions (EF), and cardiac output (CO). The assessments of the tests will be performed at three time points (before exercise, at the end of exercise, and 6 weeks after exercise). Adverse events will be recorded faithfully during the study.

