### Trial design {8}

This study will be a multicenter, single blind (assessor and statistician), 19-week, randomized parallel control group trial. Patients will be allocated in a 1:1 ratio into the control group or Tai Chi group.

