## Assignment of interventions: allocation

### Sequence generation {16a}

Participants will be randomly assigned to the control group or Tai Chi group (1:1) via block randomization at baseline using a central stochastic system.

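### The A/B labels meant to blind the statisticians are decoded in the protocol itself, and the concealment section leaves assessor blinding unsecured

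*Protocol article*

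**What the plan says.** All references are to the protocol article.

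- **The claim of blinding.** The abstract's Methods paragraph says: "This is a parallel-design, two-arm, analyst assessor-blinded, randomized controlled trial". Trial design {8} repeats it: "single blind (assessor and statistician".
- **How it is to be achieved.** Who will be blinded {17a} accepts that participants and coaches cannot be blinded, and then names two measures. One is restricted access: "study personnel, such as researchers who perform relevant tests and outcome evaluators, will not have permission of a central stochastic system". The other is coding: "Group A will be used to identify the control group, and group B will be used to identify the Tai Chi group", to which the sentence adds "thus blinding the statisticians and outcome evaluators".
- **When the code is broken.** Procedure for unblinding {17b} places disclosure of the allocation after the statisticians have finished both data management and analysis.
- **Concealment.** Concealment mechanism {16b} consists of one sentence: "Allocation is not concealed and will be revealed to both the participants and the researcher upon randomization".
- **How allocation is issued.** Sequence generation {16a} says participants are assigned "via block randomization at baseline using a central stochastic system". Implementation {16c} gives the system login to dedicated staff at each hospital and adds: "Patients will receive a unique random number from random staff".

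**The concern.** A group code masks an analyst only if the analyst does not know what it stands for. Here the code and its key are in one sentence of a published document that a trial statistician would be expected to read. The step in {17b} then has nothing left to reveal.

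The second difficulty is one of wording. {16b} discloses the allocation to the researcher, without saying which one. {17a} uses the same noun for the people who run the tests and are supposed not to know the allocation. {16b} also answers the item on allocation concealment by saying there is none, although {16a} and {16c} describe a central system that could provide it.

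This matters because participants and coaches know the allocation, so masking of testers and analysts is the main protection left. Reaching VO2peak depends on the participant's maximum effort ({12}). The analyst, on the text shown, also has choices to make: {20a} lets the data decide between a t test and a nonparametric test and runs both ITT and per-protocol comparisons, {20b} plans age subgroups without cut-points, and {20c} says only that missing-data patterns will be examined. An analysis plan may settle these choices, and their absence here is not part of this point. They show why it matters that whoever makes them does not know which arm is which.

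**Working it through.** No sample size, power or error rate is involved, so there is nothing to calculate. The check sets the sections side by side for each party.

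**Statisticians**

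1. Claim: blind (abstract, {8}, {17a}).
2. Measure named for them: the A/B labels in {17a}. No other is named.
3. Does it work? The label takes two values, and {17a} gives the meaning of both. A reader of {17a} can therefore translate every labelled record, up to all 226 planned participants.
4. Consistency with {17b}: that section assumes the allocation is still unknown when the analysis ends. With the key printed, it is not. The claim and the mechanism cannot both stand.

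**Testers and outcome evaluators**

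1. Claim: blind (abstract, {8}, {17a}).
2. Measures named: no access to the randomisation system, and the A/B labels.
3. The first measure does not depend on the labels and is supported by {16c}, where separate staff hold the login. The second fails in the same way as for statisticians, but only if an evaluator is shown a label. The article does not say that evaluators see one for each patient. They have no need of one to run a test or score a form.
4. Consistency with {16b}: the allocation goes to the researcher, who is undefined. If that means the enrolling or treating researcher, {16b} and {17a} are compatible. If it includes those who perform the tests, they contradict each other, and denying system access does not help someone who is told the result anyway. The text does not settle which is meant.

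**Concealment before assignment**

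1. {16b} says there is none.
2. Its own timing refers to disclosure at the moment of randomisation, that is, once the assignment exists. Concealment concerns what is known before that moment.
3. {16a} and {16c} describe a central system with restricted logins, which could keep the next allocation hidden.
4. So either {16b} has confused open-label disclosure with lack of concealment, or it means what it says and the main benefit of the central system has been given up. Both readings call for a correction, but a different one in each case.

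**The case against.** The strongest reply is that the finding reaches only as far as the statisticians. Evaluators have a safeguard that does not rest on the labels, dedicated staff hold the logins, and {16b} can be read as describing an ordinary open-label trial in which the assignment is known once made. That reply stands, and it limits the point in several ways.

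- A reader might infer that **assessor blinding has failed**. The article does not show this. It shows an undefined term and a decodable label that evaluators may never see.
- A reader might infer that **recruiters can foresee the next assignment**, particularly with block randomisation. Nothing in the article says so, and the central system is compatible with a hidden sequence.
- A reader might infer that **baseline tests could be done after disclosure**, since {16a} says only that randomisation takes place at baseline. That would be an argument from silence. The schedule (Table 2) and the flow chart (Fig. 1), where the order would normally appear, are not shown.
- A reader might suppose that **unblinded testers would encourage one arm more**, or try to express the bias in ml/kg/min. The article does not mention encouragement, calls VO2peak objective and highly reproducible, and gives no input from which to derive a shift.
- SF-36 relies on the answers of participants who know their arm. Masking testers and analysts cannot remove that influence.

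It could also be said that the restricted-access sentence gives testers and evaluators only as examples, so statisticians may be covered too. Even so, lack of system access does not mask someone who analyses data labelled A and B and has the key in the protocol. That part of the finding is unaffected.

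**Conclusion.** The point holds at two strengths.

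**Established:** the analyst blinding claimed in the abstract and {8} is not delivered by the method in {17a}. The failure covers every record labelled A or B, for anyone who has read the protocol. It is an error in what the document states, not a detail left to a fuller one. It rests on one assumption: that the labels in the analysis data are the ones printed in {17a}.

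**Unsecured, not shown to be lost:** assessor blinding and concealment before assignment. {16b} conflicts on its wording with {17a} and fits badly with {16a} and {16c}, but readings exist under which both protections are intact. The sponsor has to say which reading applies.

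The effect on the estimated treatment difference cannot be quantified from the document, and no figure is offered. The printed key must be corrected, because the stated method cannot achieve its stated purpose. Correcting {16b} belongs in the same amendment.

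**What to change.** **{17a}.** Delete the statement of what A and B mean. State that testers and evaluators work from patient IDs only and see no group label. State that at database lock someone independent of the analysis replaces the existing labels with new arbitrary ones and keeps the key outside the protocol and the analysis files until the primary analysis is signed off. {17b} then has something to uncover. Fields that exist in one arm only, such as the Tai Chi training log described in {11a}, should be kept out of the blinded dataset, or they will identify the arm again.

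**{16b}.** Replace the sentence with three statements:

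1. what the central system has actually done for patients already randomised. The trial started on 1 September 2020, so the text must not assert concealment that has not been confirmed;
2. that the next allocation stays hidden until the patient is enrolled;
3. who learns the allocation after that, by role, excluding testers, evaluators and statisticians.

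**Cost.** A wording amendment submitted under {25}, one relabelling step at database lock, and a factual check with the sites and the system's administrator on how allocation has been handled so far. The central system and site randomisation staff already exist. Sample size, outcomes and tests are unchanged. If the check shows that evaluators or statisticians already knew the allocation, rewording cannot restore the blind, and the trial report should say who knew and from when.

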### Procedure for unblinding if needed {17b}

When statisticians complete the work of data management and data analysis, the random allocation will be uncovered.

## Data collection and management

### Plans for assessment and collection of outcomes {18a}

Baseline characteristic data will be collected from electronic personal medical records and recorded with an electronic case report form (eCRF) using Xi Yuan Hospital EDC. All serum samples will be subjected to laboratory tests. All data acquired during the study will be anonymized and saved in a study folder on our protected research server.

### Plans to promote participant retention and complete follow-up {18b}

The importance of completion of all trials will be informed. The participants will be able to stop at any time by themselves without giving a reason. At each point in the trial, all patients will be prompted to complete the assessments by telephone or WeChat.

### Data management {19}

The evaluators will record the data on the paper case report form, and the complete test report will be attached. The data entry personnel of each hospital will be input into the eCRF once a week and managed by independent organization.

### Confidentiality {27}

To protect information confidentiality, participants will be identified only by acronyms, and their real names will not appear on any reports during the study. Each hospital has an exclusive data administrator who will be the only person with access to the eCRF.

### Plans for collection, laboratory evaluation, and storage of biological specimens for genetic or molecular analysis in this trial/future use {33}

At baseline, week 12 and week 19, 10 ml blood from participants will be collected, and blood will be isolated at 3000 r/min for 10 min. After the serum entered the frozen pipe, it was stored in a refrigerator at − 80 °C. Independent organization will test serum biochemicals uniformly.

## Statistical methods

### Statistical methods for primary and secondary outcomes {20a}

Statistical analysis will be performed by statisticians who come from the third term using SPSS 20.0 software for Windows. Categorical variables will be expressed in terms of frequency or percentage, and continuous variables will be expressed in terms of mean and standard deviation. Primary and secondary outcome data collected after 13 weeks and 19 weeks will be compared with baseline data, respectively. For normally distributed variables, a *t* test will be used for statistical comparisons between groups. If it is nonnormal, then a nonparametric test is used. *P* values less than 0.05 will be considered statistically significant. To verify that the results are consistent, the primary outcome (change in VO_2Peak_ between baseline and 19 weeks) will be compared between the two groups using intention-to-treat (ITT) and per-protocol subject analysis (PPS). The Pearson correlation or Spearman correlation measures the correlation between two variables.

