### Sample size {14}

Sample size estimation in this trial is based on the expected improvement of VO_2Peak_ in 12 weeks of Tai Chi training in patients with heart failure [31]. After 12 weeks of intervention, the VO_2Peak_ of the aerobic exercise group and Tai Chi group was respectively 13.0 ± 4 ml/kg/min and 15.2±6 ml/kg/min. We set *α* = 0.05, *β* = 0.10. The sample size will be estimated according to the estimation formula:
$$ {n}_1={n}_2=2{\left[\frac{\left({t}_{2a}+{t}_{2\beta}\right)\;s}{\delta}\right]}^2 $$

It is estimated that a sample size of 94 participants per group will be required. Considering a 20% dropout and exit rate, we will recruit 226 participants, with 113 participants in each group.

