### Methods in analysis to handle protocol non-adherence and any statistical methods to handle missing data {20c}

Missing data patterns will be analyzed by means of missing value analyses.

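### As written, the week-13 result of a patient lost before week 19 does not inform the primary VO2peak comparison, and no missing-data method supplies a value

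*Protocol article*

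**What the plan says.** The abstract of the protocol article sets the visits: "The assessments of the tests will be performed at three time points (before exercise, at the end of exercise, and 6 weeks after exercise".

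Section {20a} (statistical methods for primary and secondary outcomes) treats the two follow-up visits one at a time: "Primary and secondary outcome data collected after 13 weeks and 19 weeks will be compared with baseline data, respectively". The between-group method is: "For normally distributed variables, a *t* test will be used for statistical comparisons between groups", with a nonparametric test otherwise. The same section defines the primary outcome as the change in VO2peak from baseline to week 19, which "will be compared between the two groups using intention-to-treat (ITT) and per-protocol subject analysis (PPS").

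Section {20c} is the item for non-adherence and missing data. It consists of one sentence: "Missing data patterns will be analyzed by means of missing value analyses". The article names no imputation, carry-forward rule or repeated-measures model.

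Section {14} (sample size) plans for loss: "Considering a 20% dropout and exit rate, we will recruit 226 participants", 113 per group.

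**The concern.** A t test or rank test on change to week 19 can use only patients who have a week-19 value. Someone who completes training, is tested at week 13 and is then lost in the 6-week follow-up drops out of the primary comparison. That patient's week-13 change is likely to be a good predictor of the missing value, yet the stated method cannot use it. The ITT label says who should be analysed, but does not supply a value for a patient who has none.

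Two things are at stake. The smaller is precision. The larger is bias: the primary endpoint falls after training has ended, and patients know their arm, so late loss could be related to response and could differ between arms. The article cannot show whether it will.

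**Working it through.** **1. The plan's own figures.** Section {14} gives an outcome that "was respectively 13.0 ± 4 ml/kg/min and 15.2±6 ml/kg/min" and "We set *α* = 0.05, *β* = 0.10". The difference is 15.2 − 13.0 = 2.2, and the pooled SD is √((4² + 6²)/2) = √26 = 5.10.
- One-sided α of 0.05 gives n = 93 per group, close to the stated 94. Two-sided α gives 113 (normal) or 114 (t). The article does not state the sidedness.
- Recruitment: 94 × 1.2 = 112.8, so 113 per group, as stated.

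**2. Who has a week-19 value.** At 20% loss, 113 × 0.8 = 90.4 per group remain. The other 22.6 per group (about 45 in all) leave the primary comparison. Only those lost after week 13 have a week-13 result that goes unused, and the article does not say how many they are.

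**3. Precision under random loss.** Let n13 and n19 be the numbers per group seen at each visit, and ρ the correlation of the two changes. A likelihood model using both visits has variance at week 19 of

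(σ²/n19) × [1 − ρ² × (1 − n19/n13)].

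The effective n is n19 divided by the bracket. ρ and the timing of loss are assumptions. Two-sided power for 2.2 takes the SD of change as 5.10.

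| Share of losses seen at week 13 | n13 | Effective n, ρ 0.3 to 0.9 | Two-sided power |
|---|---|---|---|
| t test only | – | 90.4 | 82.7% |
| a quarter | 96.0 | 90.9 to 94.9 | 82.9% to 84.4% |
| half | 101.7 | 91.3 to 99.3 | 83.0% to 86.0% |
| all | 113 | 92.1 to 107.9 | 83.3% to 88.7% |

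Example (all seen, ρ 0.9): 90.4 / (1 − 0.81 × 0.2) = 90.4 / 0.838 = 107.9. The gain is 0.2 to 6 points of power.

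Suppose instead 10% are lost before week 13 and 11% of the rest afterwards (0.10 + 0.90 × 0.11 = 19.9% in all). The standard-error ratio is then √(1 − 0.11ρ²): 0.980 at ρ = 0.60 and 0.959 at ρ = 0.85, a fall of about 2% to 4%.

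**4. Bias under selective loss.** Simulation: 6,000 trials per scenario, 113 per arm, no true difference, loss split as just described. Late loss is random in controls. In the Tai Chi arm it depends on the week-13 change at log-odds −1.5 per SD. All of these inputs are assumed.

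| SD of change, ρ | Bias of week-19 t test (ml/kg/min) | Type I error |
|---|---|---|
| 4.0, 0.60 | 0.32 | about 8% |
| 4.0, 0.75 | 0.40 | about 10% |
| 5.1, 0.85 | 0.56 | about 12% |

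Simulation error on a 12% rate is √(0.12 × 0.88/6,000), or 0.4 points. As a cross-check of the middle row, bias/SE = 0.393/0.584 = 0.67, and P(Z > 1.29) + P(Z < −2.63) is about 10%.
- At half that strength (−0.75 per SD), bias is 0.18 to 0.33 and type I error 6% to 7%.
- The likelihood estimate using week 13 stays within about 0.02 of the truth.
- If loss depends on the unseen week-19 value, the t test is biased by 0.52 to 0.70 and the model by 0.23 to 0.37.

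**The case against.** The strongest reply is that this is a condensed article. It names ITT, nowhere says that patients with missing values are excluded, and leaves room for a separate analysis plan to say how ITT is met. A t test on change is also a simple and valid two-arm method. Part of this stands: an unseen plan could add imputation, so the point holds only for the methods as written. But {20a} does fix the test, and {20c} fills the missing-data item with a step that yields no estimate. That is a choice that can be bettered, not merely an omitted detail.

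Three stronger readings are tempting and not supported:
- A reader might infer that every lost patient's week-13 result is thrown away. Patients lost before week 13 have none, and with training five times a week for 3 months much of the loss may fall there. Those lost later still count in the planned week-13 comparison.
- A reader might infer that the primary result will be biased. The selective-loss mechanism is hypothetical. Nothing in the article suggests one-arm selection: controls train for matched time, frequency and intensity, and section {18b} has all patients prompted to complete assessments. The scenario is also the kind under which the model is unbiased by construction.
- A reader might take a larger bias, 25–44% of the planned 2.2, by assuming 20% late loss in the Tai Chi arm against 11% in controls. That implies 0.10 + 0.90 × 0.20 = 28% total loss in that arm against 19.9% in controls, about 24% overall, which exceeds the protocol's own 20%.

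**Conclusion.** The point holds in limited form. Under {20a} and {20c} as written, the primary week-19 comparison takes no information from the week-13 result of patients lost in between, and ITT is named without a method that could deliver it.

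The size depends on what is not known. With random loss the cost is only a slightly larger standard error. With one-arm loss driven by week-13 response, the assumed inputs give a bias of roughly a tenth to a quarter of the planned difference (0.2/2.2 = 9%; 0.6/2.2 = 27%), and a repeated-measures model removes it. With loss driven by the unseen week-19 value, the model leaves about half of the bias or somewhat less (0.23 to 0.37 against 0.52 to 0.70). The case for change is therefore cheap protection against a plausible bias, not a demonstrated error in the trial's result.

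**What to change.** In {20a} and {20c}, make the primary VO2peak analysis, and likewise that of SF-36, a mixed model for repeated measures:
- Outcome: change from baseline at weeks 13 and 19, which keeps the stated endpoint.
- Fixed effects: arm, visit, arm-by-visit, baseline value and baseline-by-visit, with an unstructured covariance.
- Patients: all randomised patients with any follow-up value.
- Primary estimate: the arm contrast at week 19.

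Keep the t test as supportive. Add one sensitivity analysis that assumes worse outcomes for missing patients and includes those with no follow-up value, whom the model alone leaves out. Settle the wording before allocation is uncovered.

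The cost is revised text and slightly more analysis work, with no new patients, visits or measurements. SPSS, the software already named, can fit the model. The downside is the assumption that loss depends only on observed data, which the sensitivity analysis is there to test.

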### Interim analyses {21b}

There are no interim analyses planned.

